### Specific objectives and hypothesis

The primary research objective of the Be Healthy in Pregnancy (BHIP) study is to determine whether introducing a structured and monitored nutrition (high-dairy protein diet) and exercise (walking) program (intervention) in early pregnancy, compared to standard prenatal care (control), will increase the number of women attaining GWG (outcome) within the Institute of Medicine (IOM) recommendations for their pre-pregnancy body mass index (BMI) sub-category [17].

Secondary objectives include determination of the impact of a maternal high-dairy diet with exercise compared to standard care diet during pregnancy on: (1) bone status (e.g. blood biomarkers procollagen type I that contains N-terminal extensions (PINP), C-terminal telopeptide of type I collagen (CTX-I), insulin-like growth factor-1 (IGF-1), 25-hydroxyvitamin D (25(OH)D), and 1,25-dihydroxyvitamin D) in mothers during pregnancy; (2) infant bone status at birth via cord blood; and (3) mother and infant bone status at six months postpartum by dual energy x-ray absorptiometry (DXA) scan.

The over-arching hypothesis is that maternal consumption of a high-dairy diet during pregnancy will have a positive impact on: (1) GWG; (2) bone health status of the mother during and after pregnancy; and (3) bone mass and bone size of the offspring, after adjustment for factors known to influence skeletal status.

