## Methods/design

### Trial design

The BHIP study is a two-arm, two-site prospective RCT. This study is designed as a prospective superiority trial, with 1:1 allocation ratio to either the Intervention group (i.e. Nutrition + Exercise intervention: high-dairy nutrition intervention combined with structured exercise) or the Control group (i.e. usual care as per National Health Canada recommendations) during pregnancy. The study is open-label with blinded endpoints. The study protocol is described following the standard protocol items: recommendations for interventional trials (SPIRIT) guidelines [34]. See Additional file 1 for the SPIRIT checklist and Additional file 2 for the WHO trial registration data set.

The core BHIP trial follows women up to delivery as the primary outcome relates to GWG. The Bone-BHIP study is an extension of the core BHIP trial that continues a follow-up of the women and their offspring until six months after delivery, with the objective to assess maternal and infant bone status. This trial is registered at ClinicalTrial.gov (NCT01689961). The BHIP trial is conducted by collaborative research teams at McMaster University (Hamilton, ON) and Western University (London, ON) in Canada. The study takes place in academic hospitals and community healthcare clinics in London, Burlington, and Hamilton, Ontario, Canada. Recruitment is facilitated by healthcare professionals (e.g. family doctors and midwives) who ask their patients for consent to be contacted by the BHIP study team, as well as poster advertisements in midwifery, family practice, and ultrasound clinics, at community sites such as the YMCA, libraries, and coffee shops, and on Facebook or Kijiji.

Study recruitment began in January 2013 and is expected to be completed by April 2018, reaching the a priori calculated sample size of 242 participants for our primary outcome. All participants who sign consent to contact forms receive a phone call by study personnel and are provided a general overview of the study and expectations using a scripted text. Figure 1 outlines the participant’s timeline in the BHIP study. Participants are screened for eligibility during the telephone interview according to the criteria list below. Eligible women are enrolled in the study and sign informed consent by the end of the first trimester of pregnancy (i.e. 12–17 weeks of gestation).

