## Outcome measurements

Primary and secondary outcomes are summarized in Table 2 and described below.Primary outcome○ GWGSecondary outcomes○ Maternal and cord blood circulating bone markers: PINP, CTX-I, IGF-1, 25(OH)D, 1,25dihydroxyvitamin D○ Maternal bone status at six months postpartum: whole-body bone mineral content (BMC), whole body BMD, lumbar spine BMD○ Infant bone status at six months of age: whole body minus the head BMCOther outcomes○ Maternal body weight and fat mass○ Maternal metabolic status (including fasting glucose and lipid profiles, leptin and adiponectin)○ Maternal blood pressure○ Maternal pregnancy outcomes such as gestational diabetes and pre-eclampsia○ Infant birth outcomes such as birth weight and body fat mass at six months○ Safety outcomes○ Quality of life using the EQ-5D questionnaire○ Healthcare costs○ Maternal and cord blood gene variant profiles

**Table 2 Tab2:** Analysis plan: objectives, outcomes, hypotheses, and methods of analysis

Objective	Hypothesis	Outcome measure (type of outcome: B = binary or C = continuous)	Methods of analysis
1. Primary	An experimental combined Nutrition + Exercise intervention will increase the percentage of pregnant women who achieve GWG within current recommendations when compared with standard care provided in the primary care community setting	Proportion of women who are within the BMI appropriate GWG according to the IOM guideline for GWGs (B)	Logistic regression
2. Secondary	An experimental combined Nutrition + Exercise intervention will lead to better maternal and child bone health outcomes when compared to standard care	*• Maternal and cord blood circulating bone markers (C)* ○ Bone biomarkers: PINP, CTX-I, IGF-1, 25(OH)D, 1,25(OH)_2_D *• Maternal bone status at 6 months postpartum (C)* ○ Whole body bone mineral content, whole body BMD, lumbar spine bone mineral density by DXA scan *• Maternal fat mass (C)* *• Maternal blood glucose, lipid profile, leptin, and adiponectin* *• Maternal blood pressure (C)* ○ Diastolic BP ○ Systolic BP *• Maternal pregnancy outcomes (B)* ○ Gestational diabetes ○ Pre-eclampsia *• Infant bone status at 6 months of age (C)* ○ Whole body minus the head bone mineral content by DXA scan *• Infant outcomes* ○ Birth weight z-score(C) ○ Body fat mass (B)	Regression analysis *We will use logistic regression for binary outcomes and linear regression for continuous outcomes

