Fasted maternal blood samples for metabolic and bone health biomarkers are collected at 12–17 weeks of gestation, 36–38 weeks of gestation, and at six months postpartum; venous cord blood is collected at delivery. Serum is collected in serum-separating with gel (SST™) vacutainers and in spray-coated silica vacutainers; plasma is collected in sodium fluoride/ Na_2_ ethylenediaminetetraacetic acid (Na2EDTA) vacutainers. Sample are centrifuged for 10 min at 3000 rpm at 4 °C; serum separator tubes are spun for an additional 5 min, aliquoted, and stored at − 80 °C. Samples are batched to include all samples from each mother for analysis in our laboratories when participants have completed the study. Fasting plasma glucose is determined using a hexokinase photometric assay (Architect kit, Abbott, Abbott Park, IL, USA). Serum triglycerides are analyzed using a glycerol phosphate oxidase photometric assay (Architect kit, Abbott, Abbott Park, IL, USA) completed by Hamilton Health Sciences Regional Laboratory Medicine Program. Serum leptin and insulin are analyzed using Luminex® human premixed multi-analyte enzyme-linked immunosorbent assay (ELISA) kit supplied by R&D Systems (Minneapolis, MN, USA). Serum adiponectin and C-reactive protein are analyzed by Luminex® premixed multi-analyte ELISA kit supplied by R&D Systems. Bone formation is assessed by measuring serum PINP by ELISA (Cloud Clone Corp., Houston, TX, USA). Bone resorption is assessed by measuring serum CTX-I by (Serum Crosslaps (CTX-1) ELISA, product code AC-02F1 Immunodiagnostic Systems, UK). Growth is assessed by measuring serum IGF-1 by ELISA (R&D Systems, Minneapolis, MN, USA). All standards and samples are analyzed in duplicate, following the manufacturer’s instructions. A serum quality control is run in triplicate at the beginning and end of each ELISA plate to calculate inter- and intra-assay coefficients of variability. Serum vitamin D metabolites are measured by liquid chromatography tandem mass spectrometry (LC-MS/MS) using a Waters AQUITY Tandem Quadropole Detector coupled to an AQUITY UPLC system (Waters Corporation), after extraction that includes a saponification step as adapted from Hymoller [47]. Accuracy is determined using the certified Vitamin D analytes serum-based standard reference material (SRM 972a) from the US National Institute for Standards and Technology (NIST; National Bureau of Standards, Washington, DC, USA) [48]. Precision is measured using a serum quality control in all runs of samples tested, allowing calculation of inter- and intra-assay coefficients of variability.

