### Statistical methods

The analysis and reporting of the results will follow the SPIRIT statement for reporting RCTs [53]. The process of patient selection and flow throughout the study will be summarized using a flow-diagram (Fig. 2).

The results of patient baseline characteristics and outcome variables (both primary and secondary) will be summarized using descriptive summary measures: expressed as mean (standard deviation) or median (range) for continuous variables and n (%) for categorical variables. All statistical tests will be performed using two-sided tests at the 0.05 level of significance. Binary outcomes will be analyzed using logistic regression and continuous outcomes will be analyzed using linear regression. All analyses will account for stratification by including study site and participants’ BMI category in the models. For all models, the results will be expressed as estimate of the difference for continuous outcomes (odds ratio [OR] or relative risk [RR] for binary outcomes), corresponding two-sided 95% confidence intervals (CI) and associated *p* values. *P* values will be reported to three decimal places with values < 0.001 reported as < 0.001. The Hosmer–Lemshow will be used to assess goodness-of-fit for logistic regression and explore the residuals to assess goodness-of-fit and model assumptions for linear regression.

An intention-to-treat principle will be adopted to analyze all outcomes. Multiple-imputation will also be used to handle missing data during data collection. Sensitivity analyses will be performed using some of the commonly used RCT patient-level methods (e.g. generalized estimating equations, the random-effect model which account for the potential correlation within sites, etc.) to assess the robustness of the results [54]. All the analyses will be done using SAS 9.2 (Cary, NC, USA) or SPSS 13 (Chicago, IL, USA). Table 2 provides a summary of the planned methods of analyses for each outcome and subgroup.

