The secondary outcome of bone status was selected due to the emerging evidence of risk of osteoporosis in later life being programmed from the womb [24]. Bone biomarkers were selected as outcomes following the International Osteoporosis Foundation and the International Federation of Clinical Chemistry and Laboratory Medicine recommendations, which is to measure a marker of bone formation and a marker of bone resorption to assess bone turnover [66]. Currently, the most sensitive markers recommended are subgroups of type I collagen representing the predominant component of the bone matrix wherein sub-products can be measured as markers of formation and resorption of the bone [66]. To support fetal bone growth, pregnant women undergo bone metabolic adaptations over the course of pregnancy, where bone resorption usually rises and formation declines [67]. These changes result in high bone turnover during pregnancy [68]. Maternal bone turnover peaks during the third trimester, with a marked increase in bone resorption observed at 38 weeks of gestation [69]. Based on this knowledge, two biomarkers of bone modelling are quantified in maternal blood at 36–38 weeks of gestation and in cord blood. The marker of bone formation is PINP and the marker of bone resorption is CTX-I. Blood samples are consistently collected in a fasted state and in the morning, as suggested by the National Bone Health Alliance [70]. In addition, vitamin D status is measured by serum 25(OH)D as it plays an important role in calcium homeostasis and bone metabolism [71] and is a reflection of dietary vitamin D intake and sun exposure. Both the frequency of milk consumption and sun exposure were shown to be positive predictors of serum 25(OH)D concentrations in the recent multivariate analysis of three cycles of the Canadian Community Health Measures surveys [72]. The active form of vitamin D, 1,25dihydroxyvitamin D, is also measured since it is known to be upregulated during pregnancy [73].

Bone mineral content was selected as an outcome because it is linked to the peak bone mass (i.e. highest bone mass accrued for an individual) and is predictive of osteoporotic fracture [32]. Furthermore, recent evidence suggests that childhood BMC persists until peak bone mass and could indicate individuals at risk of osteoporotic fracture [31].

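### The stated model for 25(OH)D names no season term, although the article says this marker reflects sun exposure; the cost is precision, not bias.

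*Protocol article*

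**What the plan says.** All places are in the protocol article.

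- **Outcome.** Outcome measurements lists among the secondary outcomes: "Maternal and cord blood circulating bone markers: PINP, CTX-I, IGF-1, 25(OH)D, 1,25dihydroxyvitamin D".
- **Model.** Statistical methods says that "continuous outcomes will be analyzed using linear regression" and, on covariates, "All analyses will account for stratification by including study site and" BMI category. Table 2 adds one outcome-specific covariate, feeding type, for infant growth at six months. Neither place mentions season or date of sampling.
- **Determinants of 25(OH)D.** The Discussion describes the marker as reflecting vitamin D from diet and from the sun, and reports from national survey data: "Both the frequency of milk consumption and sun exposure were shown to be positive predictors of serum 25(OH)D concentrations".
- **Sampling.** Data and biosample collection: "Fasted maternal blood samples for metabolic and bone health biomarkers are collected at 12–17 weeks of gestation, 36–38 weeks of gestation", with a further maternal sample six months postpartum and cord blood at delivery.
- **Calendar span.** Trial design: "Study recruitment began in January 2013 and is expected to be completed by April 2018". The sites are in Ontario.
- **Allocation.** Randomization is 1:1 in random blocks of two, four and six, stratified by site and BMI category.

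**The concern.** The intervention raises dairy intake, and 25(OH)D is the marker closest to that mechanism. The article names two predictors of it. One, milk, is what the trial manipulates. The other, sun exposure, varies with the time of year and goes into the residual unless it is modelled. Women are sampled in every season, so this variation will be present in the data.

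Seasonal noise widens the confidence interval for the arm difference and lowers the chance of detecting a real dairy effect. The marker also has to meet a Bonferroni-adjusted threshold under Table 2. Season is easy to model: it follows from the calendar date of sampling and needs no new measurement. Table 2 shows that the authors do name outcome-specific covariates in the article where they saw a need.

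**Working it through.** **1. The plan's own figure.** Power calculation gives a total of 177 for the maternal bone biomarkers (two-group t-test, alpha 0.05, beta printed as 20 and read here as 20%, 15% attrition). It prints no difference or SD, so 177 cannot be derived directly. Working backwards, 75 per arm gives 150 / (1 − 0.15) = 176.5, rounded up to 177. The implied standardized difference is d = (1.960 + 0.842) × √(2/75) = 0.457. I use it as the base case with 80% power.

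**2. Adding season to the stated model.** Let R² be the share of 25(OH)D variance explained by season. This is assumed, as the documents give no figure. The residual SD is multiplied by √(1 − R²), and power = Φ(2.802/√(1 − R²) − 1.960).

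| R² | SE multiplier | Power at alpha 0.05 | Total N for 80% power |
|---|---|---|---|
| 0 | 1.000 | 80.0% | 177 |
| 5% | 0.975 | 82.0% | 170 |
| 10% | 0.949 | 84.0% | 160 |
| 15% | 0.922 | 86.0% | 151 |
| 20% | 0.894 | 87.9% | 142 |
| 30% | 0.837 | 91.8% | 125 |

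Over 5–20% the gain is about 2–8 points; at 30% it is about 12.

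**3. A stricter threshold.** The article does not say how many tests enter the Bonferroni correction. As an illustration only, five markers give alpha = 0.01, with 2.576 in place of 1.960. Power is then Φ(2.802 − 2.576) = 58.9% without season, 61.7% at R² = 5% and 71.1% at R² = 20%, a gain of about 3–12 points.

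**4. Bias and type I error.** A simulation used stratified random blocks of 2/4/6, uniform accrual over 5.25 years, a sinusoidal season effect, about 150 women analysed and 1,500 runs per scenario, with R² at 10%, 20% and 30%. Without a season term the mean arm difference was 0.455–0.461 against a true 0.457, type I error was 4.7–5.5% and power was 79–81%. With the term, power was 83%, 87% and 90%. This agrees with step 2 and shows no bias.

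**5. If baseline 25(OH)D were also used (not stated in the article).** The two pregnancy samples are 36 − 17 = 19 to 38 − 12 = 26 weeks apart. On a yearly cycle their seasonal parts correlate cos(2π × 19/52.18) = −0.66 to cos(2π × 26/52.18) = −1.00, about −0.88 on average. With seasonal share s and non-seasonal correlation r between visits (both assumed), residual variance is 1 − (r(1 − s) − 0.88s)² with baseline alone, and (1 − s)(1 − r²) with baseline and season.

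- s = 5%, r = 0.5: 0.814 against 0.712, a cut of 12.5%.
- s = 20%, r = 0.7: 0.853 against 0.408, a cut of 52%.

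For a change score at s = 10%, r = 0.6, the variance is 2(0.9)(0.4) + 2(0.1)(1.88) = 1.10, against 0.72 once season is removed.

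**The case against.** The strongest objection is that this is a condensed article, and a prognostic covariate for one of five secondary biomarkers is ordinary content for an analysis plan that is not shown. That stands as a limit on severity: the article does not forbid a season term, and the plan may already contain one. The point survives as a recommendation because the article does state the model for continuous outcomes, and a nearly costless addition that its own Discussion motivates would improve it.

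A reader might infer four stronger things that the documents do not support.

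- **That season confounds the comparison.** It does not. Concurrent 1:1 allocation in small blocks balances calendar time in expectation, and chance imbalance is already in the standard error (step 4).
- **That the models hold only arm, site and BMI category.** The sentence says how stratification is handled and is not a closed list. The feeding-type footnote in Table 2 shows that other covariates can enter.
- **That the hypothesis is contradicted.** The phrase "after adjustment for factors known to influence skeletal status" is unspecific and closes the item on offspring bone mass and size. It does not clearly reach maternal 25(OH)D.
- **That the near half-year gap between samples harms the planned analysis.** Both arms are sampled at the same gestational ages, so a comparison at 36–38 weeks is unaffected. The gap, and the 12.5–52% figures in step 5, matter only with a baseline covariate or a change score.

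**Conclusion.** The point holds as a minor one about efficiency. The stated model for 25(OH)D names no season term, the article itself identifies sun exposure as a determinant, and sampling covers all seasons. Validity is intact.

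The size rests on the assumed 5–20% seasonal share and on the back-solved difference of 0.457. The larger gains in step 5 also need an assumed between-visit correlation and an analysis that the article does not describe, so they should not be quoted as the cost of the present plan. The primary outcome is not touched.

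**What to change.** Add one sentence to the analysis plan. For maternal 25(OH)D at 36–38 weeks and at six months postpartum, and for cord 25(OH)D, the linear regression will include the calendar date of sampling as one sine/cosine pair (or a four-level season factor), alongside arm, site and BMI category. If baseline 25(OH)D or change from baseline is used, keep the season term in that model too.

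The actual draw date is known only after randomization, and for cord blood it is the delivery date. If a strictly pre-randomization covariate is wanted, use the date expected from gestational dating, which for cord blood is the expected delivery date.

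The cost is two degrees of freedom for the sine/cosine pair or three for the four-level factor. The article does not say that draw dates are recorded, but visits timed by gestational age make it likely, so no new data should be needed. Fixing the form in advance also avoids a choice of adjustment after the results are seen.

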### Randomization: allocation and implementation

Block randomization is used with block sizes of two, four, and six selected at random, using an online Research Electronic Data Capture (REDCap) randomization service managed by an independent team in the Biostatistics Unit at St Joseph’s Healthcare in Hamilton, ON, Canada. Randomization to the two study arms occurs in a 1:1 ratio and is stratified by study site and pre-pregnancy BMI category following IOM guidelines (underweight: BMI < 18.5, normal weight: BMI 18.5–24.9, overweight: BMI 25.0–29.9, and obese: BMI ≥ 30.0 kg/m^2^). The eligibility of participants is confirmed at the first visit, when baseline data are also collected. The research assistant randomizes the participant at the second visit to the study center using an online third-party automatic randomization system. Once randomized, the research assistant consents the participant to the appropriate study arm at a time that is 14–17 weeks/6 days of gestation. Assessments, regardless of the study arm, occur at < 18 weeks of gestation, 26–28 weeks of gestation, 36–38 weeks of gestation, birth, three months postpartum, and six months postpartum. The intervention arm consists of weekly or biweekly in-person visits (based on the participant’s preferences) during pregnancy (i.e. from allocation to study group until 36–38 weeks of gestation). Baseline measures (i.e. before randomization), primary and secondary outcome measures, and other measures assessed during and after pregnancy are measured in all participants, regardless of their study group allocation.

The flow diagram (Fig. 2) will be included in future published results.

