### Data and biosample collection

The pre-pregnancy BMI is calculated using the measured weight at study entry minus the mother’s self-reported GWG. Body weight is measured by trained research assistants using a body impedance Tanita Body Composition Analyzer BF-350 scale (Tanita, IL, USA) at 12–17 weeks of gestation, 26–28 weeks of gestation, 36–38 weeks of gestation, three months postpartum (self-reported weight only), and six months postpartum. GWG is calculated by subtracting the weight at the 36–38 weeks of gestation study visit by the pre-pregnancy weight. Adjustments such as rate of GWG will be made to account for gestational age at delivery, including pre-term births.

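### No baseline outcome value is named as a covariate for maternal outcomes sampled before and after randomization, so precision available at no cost is left unclaimed

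*Protocol article*

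**What the plan says.** On the models, Statistical methods states: "Binary outcomes will be analyzed using logistic regression and continuous outcomes will be analyzed using linear regression". On their terms it states: "All analyses will account for stratification by including study site and participants’ BMI category in the models". Table 2 repeats the model types and adds one outcome-specific covariate: feeding type, for infant growth at six months. The section on specific objectives and hypothesis mentions adjusting for influences on the skeleton but does not list them. Power calculation sizes the maternal bone biomarker outcome with a two-group t-test.

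On the data, the randomization section says: "Baseline measures (i.e. before randomization), primary and secondary outcome measures, and other measures assessed during and after pregnancy are measured in all participants". Baseline data are collected at the first visit and randomization takes place at the second. Data and biosample collection says: "Fasted maternal blood samples for metabolic and bone health biomarkers are collected at 12–17 weeks of gestation, 36–38 weeks of gestation", and adds a sample at six months postpartum. Weight is measured at the same pregnancy visits. The Discussion describes PINP and CTX-I more narrowly: "two biomarkers of bone modelling are quantified in maternal blood at 36–38 weeks of gestation and in cord blood".

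For the primary outcome: "GWG is calculated by subtracting the weight at the 36–38 weeks of gestation study visit by the pre-pregnancy weight". Pre-pregnancy BMI rests on a self-report: "The pre-pregnancy BMI is calculated using the measured weight at study entry minus the mother’s self-reported GWG".

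**The concern.** When a continuous outcome is measured before and after randomization, its baseline value is usually its strongest predictor. Leaving it out of the linear model keeps variance in the residual that could have been explained. Intervals are then wider and power lower than the collected data allow.

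The article goes down to the level of individual covariates (site, BMI category, feeding type) without naming a baseline outcome value. Efficiency matters here because the recruitment target was cut from 350 to 242 and the secondary outcomes are to be tested with a Bonferroni correction.

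The primary outcome raises a related but weaker question. Part of total gestational weight gain (GWG) has already happened when a woman is randomized. The intervention cannot alter that part, and it is not named in the model either.

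**Working it through.** **1. The plan's own figure.** Power calculation gives 177 in total for maternal bone biomarkers (1:1, alpha 0.05, beta printed as 20 and read here as 0.20, 15% attrition). No difference or SD is stated, so 177 cannot be reproduced. It can be inverted with d = (1.960 + 0.842) × √(4/N), using the normal approximation:

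- If 177 is the number analysed: d = 2.802 × √(4/177) = 0.42.
- If 177 includes the attrition, 177 × 0.85 = 150 are analysed: d = 2.802 × √(4/150) = 0.46.

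**2. Effect of adding the baseline value.** Inputs: two-sided alpha 0.05 ("All statistical tests will be performed using two-sided tests at the 0.05 level of significance"), an effect with 80% power unadjusted, and a correlation r that the article does not give and that is **assumed** here between 0.2 and 0.7. The residual SD becomes SD × √(1 − r²). Power = Φ(2.802/√(1 − r²) − z), with z = 1.960 at alpha 0.05. For Bonferroni over the five listed markers (PINP, CTX-I, IGF-1 and two vitamin D metabolites), alpha = 0.05/5 = 0.01 and z = 2.576.

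| Assumed r | 1 − r² | CI width ratio √(1 − r²) | Power, alpha 0.05 | Power, alpha 0.01 |
|---|---|---|---|---|
| 0 (no baseline term) | 1.00 | 1.00 | 80.0% | 58.9% |
| 0.2 | 0.96 | 0.98 | 81.6% | 61.2% |
| 0.3 | 0.91 | 0.95 | 83.6% | 64.1% |
| 0.5 | 0.75 | 0.87 | 89.9% | 74.5% |
| 0.7 | 0.51 | 0.71 | 97.5% | 91.1% |

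Example, r = 0.5: 2.802/0.866 = 3.235. Then Φ(3.235 − 1.960) = 0.899 and Φ(3.235 − 2.576) = 0.745.

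These powers are the same on either reading of 177, because the effect is set to give 80% at that size. If the full 242 are recruited and the 87% retention reported to 36–38 weeks holds, 242 × 0.87 ≈ 210 would be analysed. Unadjusted power at alpha 0.05 would then start higher: Φ(0.42 × √(210/4) − 1.960) ≈ 86% or, with d = 0.46, about 91%. The gain in percentage points would be smaller. The CI width ratios do not change.

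**3. Which outcomes have a baseline value.** Maternal blood markers and weight have one, subject to the Discussion's wording on PINP and CTX-I. Maternal DXA is first done at six months postpartum. Cord blood and infant measures cannot precede randomization. The table does not apply to these.

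**4. Primary outcome.** If the same pre-pregnancy weight is used for BMI and for GWG, then pre-pregnancy weight = entry weight − self-reported gain, and

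GWG = (weight at 36–38 weeks − entry weight) + self-reported gain to entry.

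The last term is fixed before randomization. A simulation gives an idea of its value as a covariate. It used 600 runs per setting, n = 210, **assumed** rates within range of 35% and 55%, and a one-sided cut on a latent gain. Power without and with the covariate was 82% and 83% at latent correlation 0.2, 81% and 85% at 0.4, and 83% and 92% at 0.6. Being within range has both a lower and an upper limit, so the real gain would probably be smaller.

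**The case against.** The strongest reply is that the article is condensed. The sentence on site and BMI category says how stratification is handled and does not close the list of covariates. The hypothesis section and the Table 2 footnote both announce further adjustment, and an analysis plan not shown could add baseline values. This stands against one tempting reading, that the models contain nothing but site and BMI category: the article does not say so. It does not remove the point. Where the article goes to covariate level it names feeding type but no baseline outcome value, and the hypothesis section commits to no particular term.

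A second reply is that a randomized comparison adjusted for its stratification factors is valid. That also stands. A reader might infer that chance imbalance at baseline biases the result, but such imbalance is sampling variation that the interval and p value already reflect. A t-test sample size is merely conservative if baseline adjustment is used later.

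Third, the correlation is unknown. The Discussion describes large changes in bone turnover by late pregnancy, so a low r is possible and the gain may be small. What counts is also the correlation left after site and BMI category, which may be lower than the raw one. Both remarks stand, and they are why the table starts at 0.2.

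Fourth, early gain is a component of GWG rather than the same outcome measured twice, and BMI category, already in the model, uses the same self-report. This stands. One might infer that the primary analysis is invalid because it counts gain from before randomization. The article does not support that: both arms are defined in the same way.

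**Conclusion.** The point holds as a missed gain in efficiency. No baseline value of a maternal outcome is named as a covariate, although pre-randomization blood samples and weights exist. For these outcomes the benefit ranges from slight (80% to about 82% power at r = 0.2) to large (97.5% at r = 0.7). Under Bonferroni over five markers it runs from about 59% to between 61% and 91%. These figures rest on an assumed correlation, an effect set at 80% unadjusted power, the normal approximation and a family of five. The article does not state the family size, and Table 2 lists more secondary outcomes than these five.

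It would be wrong to extend the point to all secondary outcomes, since maternal DXA, cord blood and infant measures have no baseline value. For PINP and CTX-I it depends on whether they are assayed at 12–17 weeks, on which two sections differ. For the primary outcome, adjustment for early gain is an option with a smaller and uncertain return.

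**What to change.** 1. Reconcile Data and biosample collection with the Discussion on whether PINP and CTX-I are assayed in the 12–17 week samples.
2. Add to Statistical methods, before unblinding: each continuous maternal outcome with a 12–17 week value is analysed by linear regression on arm, site, BMI category and its own baseline value, on the log scale where the distribution is skewed.
3. State whether self-reported gain to entry and gestational age at entry will be covariates in the primary logistic model. If so, fix their form in advance; a straight line will not do for gain, since both low and high early gain can lead out of range. Note that the odds ratio then becomes conditional on these covariates and is not directly comparable with one from a model without them.

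The cost is plan wording. No new data are needed, provided the 12–17 week samples are assayed for the markers concerned. Fixing the covariates now also prevents their being chosen after the results are seen.
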